### Statistical analysis

The primary outcome of the study is the cfPWV among HOA, HOS, and OSR (part I), and among OSR after 12 weeks of intervention with a high-intensity interval training (HIIT) and those assessed within the same time frame without the HIIT intervention (control group) (part II). To describe continuous demographic and baseline characteristics of participants in the HOA, HOS and OSR group (part I) and those in the OSR intervention and control group (part II), we will use the median and interquartile range; and for categorical characteristics, we will use percentages. Boxplots will be used to visualize the primary and secondary outcomes in the HOA, HOS and OSR group (part I) and at baseline as well as after 12 weeks in the OSR intervention and control group (part II). For part I, we will use analysis of variance to compare the cfPWV (and secondary outcomes) between HOA, HOS and OSR. For part II, we will use analysis of covariance to compare the cfPWV (and secondary outcomes) after 12 weeks between OSR in the intervention and those in the control group adjusted for the corresponding values at baseline (Vickers and Altman, 2001). For each analysis, we will report estimates (with 95% confidence intervals) of the difference in outcome between HOA and HOS and between OSR and HOS (part I), and between OSR in the intervention and those in the control group (part II). Up-to-date versions of SAS (SAS Institute Inc., Cary, NC, USA) and R (R Foundation for Statistical Computing, Vienna, Austria) will be used for analysis and graphics.

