### Sample size calculation

The sample size was calculated separately for both study parts. For part I, we assumed that the expected cfPWV corresponded to 8.5, 9.5, and 11.5 m/s for HOA, HOS and OSR, respectively, and that the standard deviation was 1.5 m/s (Tedesco et al., 2004; Gando et al., 2010). With a 2-sided significance level of 0.05, the sample size needed to attain a targeted power of 80% for detecting a difference with magnitude 1.0 m/s was 36 participants per group (the comparison between HOA and HOS) and for detecting a difference with magnitude 2.0 m/s, it was 10 participants per group (the comparison between OSR and HOS). For part II, we assumed that the expected difference in cfPWV after 12 weeks between OSR in the intervention and those in the control group was 1.0 m/s and that the standard deviation was 1.5 m/s (Madden et al., 2009). By including the baseline cfPWV (before the start of the intervention period) as a covariate in the pre-specified analysis, we will further reduce error variability and therefore assumed that the correlation between baseline and outcome cfPWV was 0.3. With a 2-sided significance level of 0.05, the sample needed to attain a targeted power of 80% for showing superiority of the intervention over control was 34 participants per group. Taking dropouts into account, we plan to include a total of 40 HOA, 40 HOS and 80 OSR. The POWER and GLMPOWER procedures in SAS 9.3 (SAS Institute Inc., Cary, NC, USA) were used for sample size calculation for the first and second study part, respectively.

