#### Potential pitfalls

Our main outcome (cfPWV) as well as most other vascular measurements are affected by age, hemodynamic variability, lifestyle behavior, and circadian fluctuations. To minimize external interference and variability, several measures are considered. Groups are matched for age and sex. Standardized vascular imaging is performed under fasting conditions in the morning after 10 min of rest in a supine position. Participants are encouraged to refrain from alcohol, caffeine and if applicable from smoking 12 h prior to the examinations. Exercise and vigorous physical activity should not be performed 24 h before the visits. The OSR group is allowed to take their medication in the morning. These measures help to minimize intra-individual as well as within-day variability.

Change of medication or start of a structured diet during the 12 week-week intervention or control condition are indications for exclusion. In addition, the start of structured exercise in the control group is considered an exclusion criterion. To prevent the start of exercise in the control group, all participants of this group are invited to take part in the voluntary supervised exercise program after the post measurements. To prevent high drop-out rates and optimize adherence to the exercise regime, every exercise session starts with strength, mobilization and coordination exercises and includes a warm-up and a cool-down. The first 2 weeks of the exercise program focus on technical and coordinative skills at lower intensities before HIIT is started in the third week into the program.

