**Figure 3 F3:**
[figure not shown]
Principle concept of the systems physiology approach.

The ExAMIN AGE Study resembles new approaches in the structural and functional diagnostics of aging processes including systems such as the vasculature, the heart, autonomic function and inflammation. The results have a focus on vascular imaging and on the non-pharmaceutical treatment of vascular health in older inactive individuals at risk. The integrative approach will help to determine the best non-invasive means to diagnose and define cardiovascular risk in advanced age and disease. This study design allows the examination of pathophysiological links between small and large arteries, the so called “vascular coupling” or “arterial cross-talk.” To date little is known about the interaction between the two vascular beds and how they affect each other. It also enables to examine the cross-talk between the vasculature and the heart. Exercise interventions can improve both entities and play a key role in the treatment of cardiovascular and metabolic diseases.

Our study has some limitations. We are aware that the recruitment of healthy older sedentary individuals (HOS) is challenging. It needs to be ascertained that all three groups are strictly matched for age. The analysis of the association of physical fitness with cardiovascular health and aging processes in the three groups represents a cross-sectional approach and is not based on prospective longitudinal data. Life-long activity is analyzed by subjective reporting but is supported by objective analysis using accelerometry and spiroergometry. The cross-sectional study design does not give evidence of a temporal relationship between physical activity exposure and physiological outcome. However, the interventional part of the study, where participants are randomly allocated to the intervention or the control group, allows for a causal and temporal analysis of the improvement of aging processes in individuals at risk. The extensive phenotyping of vascular health and other physiological systems as well as the analysis of the impact of HIIT are the main strengths and innovations of the study.

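### Part I is planned as a group-only ANOVA, although the groups are matched for age and sex and cfPWV is stated to depend on age

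*Protocol article*

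**What the plan says.** The Statistical analysis section of the protocol article gives the Part I model: "For part I, we will use analysis of variance to compare the cfPWV (and secondary outcomes) between HOA, HOS and OSR". Its products are interval estimates for two contrasts: "we will report estimates (with 95% confidence intervals) of the difference in outcome between HOA and HOS and between OSR and HOS (part I"). No covariate is named. In the same paragraph Part II is given an analysis of covariance, "adjusted for the corresponding values at baseline".

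The Potential pitfalls section says of the primary outcome: "Our main outcome (cfPWV) as well as most other vascular measurements are affected by age, hemodynamic variability, lifestyle behavior, and circadian fluctuations". Among the countermeasures it lists "Groups are matched for age and sex". The inclusion criteria admit ages 50 to 80 in every group. Among the limitations, the Discussion and conclusion section says "We are aware that the recruitment of healthy older sedentary individuals (HOS) is challenging", and adds that strict age matching of the three groups has still to be ascertained.

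The Sample size calculation section sizes Part I on expected means of 8.5, 9.5 and 11.5 m/s for HOA, HOS and OSR, "and that the standard deviation was 1.5 m/s". It arrives at 36 per group for HOA against HOS and 10 per group for OSR against HOS; 40, 40 and 80 are planned. No covariate is credited in Part I, whereas Part II takes credit for a baseline correlation of 0.3.

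**The concern.** Matching on a prognostic factor makes the groups alike on it. Between-group differences then vary less than they would between independent samples. A group-only ANOVA does not see this: the spread of cfPWV due to age stays in the error term, so the standard errors describe a less precise study than the one carried out.

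Matching may also be only approximate. A group-only model then has no means of removing what is left, and an age difference between groups is read as an effect of activity (hypothesis 1) or of cardiovascular risk (hypothesis 2).

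Hypothesis 1 is the exposed contrast. Its planned difference is 1.0 m/s with 40 per group. Hypothesis 2 has a planned difference of 2.0 m/s with 80 against 40.

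**Working it through.** **Inputs from the protocol article.** SD 1.5 m/s; differences 1.0 and 2.0 m/s; two-sided 0.05; target power 80%; planned sizes 40, 40 and 80.

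**Inputs that are assumed.** The within-group correlation r of cfPWV with the matching factors is not given, so 0.2 to 0.6 is used. The slope of cfPWV on age is taken as 0.05 to 0.10 m/s per year. With an age SD of 7 to 8.7 years (8.7 is an even spread over 50 to 80), r = slope × age SD / 1.5 runs from 0.23 to 0.58, so the two sets of assumptions agree.

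**1. The plan's own figures.** Take a pairwise contrast in a three-group ANOVA without covariates, with 3n − 3 error df and a noncentral t.
- Difference 1.0: power is 0.789 at n = 35 and 0.800 at n = 36.
- Difference 2.0: power is 0.775 at n = 9 and 0.820 at n = 10.

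The stated 36 and 10 are reproduced, so the sample size belongs to a group-only model. At 40/40/80 (157 error df) the power for hypothesis 1 is 0.84 and for hypothesis 2 above 0.99.

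**2. Precision with the matching factors in the model.** Residual SD = 1.5 × √(1 − r²). Half-width = t(0.975, df) × SD × √(1/n₁ + 1/n₂), with df 157 without and 155 with age and sex.

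Group-only, HOA-HOS: 1.975 × 1.5 × √(2/40) = 0.66 m/s. OSR-HOS: 1.975 × 1.5 × √(1/40 + 1/80) = 0.57 m/s.

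| r | Residual SD | HOA-HOS half-width | OSR-HOS half-width | Power, hypothesis 1 |
|---|---|---|---|---|
| group-only | 1.50 | 0.66 | 0.57 | 0.84 |
| 0.2 | 1.47 | 0.65 | 0.56 | 0.86 |
| 0.3 | 1.43 | 0.63 | 0.55 | 0.87 |
| 0.4 | 1.37 | 0.61 | 0.53 | 0.90 |
| 0.5 | 1.30 | 0.57 | 0.50 | 0.93 |
| 0.6 | 1.20 | 0.53 | 0.46 | 0.96 |

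The 0.84 is the planning figure, which treats the groups as independent samples. Under exact matching the estimate is already more stable than its reported standard error says. The group-only test would then detect 1.0 m/s with probability of about Φ[(1 − 0.6625)/(0.3354 × √(1 − r²))], which is 0.85 at r = 0.2 and 0.90 at r = 0.6. Against that benchmark, adjustment gains about 1 to 6 percentage points.

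**3. Direction of the error under exact matching.** The reported standard error exceeds the true one by 1/√(1 − r²): 1.02, 1.05, 1.09, 1.15 and 1.25 for r = 0.2 to 0.6. Nominal 95% intervals then cover about 95.5% to 98.6%, and the true two-sided alpha is about 0.046 to 0.014. The error is conservative.

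**4. Bias if a gap remains.** Bias = slope × difference in mean age. For 2 years: 0.05 × 2 = 0.1 m/s to 0.10 × 2 = 0.2 m/s, or 10% to 20% of the planned 1.0 m/s. A simulation of 40 against 40 with a 3-year gap and an assumed age SD of 8 years gave group-only coverage of 92% at r = 0.3, 87% at r = 0.5 and 83% at r = 0.6. The age-adjusted model stayed at about 95%.

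**The case against.** The strongest reply is that matching is itself the control for age. If it works, the group-only analysis is unbiased and errs only on the cautious side. The Part I power target is 80%, and 40 per group gives 84% without any covariate. The strength of the age dependence is not in the documents; at r = 0.3 the intervals are only about 5% too wide. All of this stands, and it sets the weight of the point.

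A second reply is that an article condenses and may leave covariates to a fuller plan. This carries less weight here. The Part I model is named, Part II receives an explicit adjustment in the same paragraph, and the Part I sample size reproduces as a covariate-free ANOVA.

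A reader might infer more than the documents support:
- **That pooling one variance over the three groups damages the HOA-HOS interval.** The article assumes a single SD of 1.5 m/s. Under it, a pooled and a separate-variance analysis have nearly the same power (84.2% and 83.8%), and nothing in the text suggests unequal SDs.
- **That Part II needs age and sex too.** Part II is randomised and already adjusts for baseline cfPWV, and the documents give no reason for more.
- **That the plan doubts its own matching.** It calls HOS recruitment challenging and strict age matching something to be ascertained. That leaves a gap possible; it does not predict one.
- **That sex is a stated driver of cfPWV.** The article names age. Sex enters only as a matching factor.

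**Conclusion.** The point holds as a free improvement. The Part I model omits the factors on which the groups are matched, one of which the article names as an influence on the primary outcome.

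The two consequences depend on how the matching turns out. With good matching, precision is given away: at most about 0.13 m/s of half-width for HOA-HOS (0.66 against 0.53 at r = 0.6), and as little as 0.01 m/s at r = 0.2. With a remaining age gap, the contrasts are biased in proportion to it. All sizes rest on the assumed correlation or slope.

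It would be wrong to conclude that Part I is underpowered, that its type I error is inflated under good matching, or that 36 and 10 per group are miscalculated. Hypothesis 2 keeps ample power in any case; for it, only the estimate and interval are affected.

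**What to change.** Specify Part I as a linear model (ANCOVA) of cfPWV, CRAE and CRVE on group, age as a continuous term, and sex. If participants are matched individually, use the matched sets in place of age and sex. Report the same two contrasts, HOA-HOS and OSR-HOS, with 95% confidence intervals from that model. State this before the data are analysed, so that covariates are not chosen after an imbalance has been seen.

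The cost is one sentence and two error degrees of freedom (157 to 155). Age and sex have to be known for the matching in any case. If age turned out to explain nothing, the t multiplier would stay at 1.975 to three decimals. The sample size need not change, and the stated 36 and 10 per group remain valid as conservative figures.

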## Cardiovascular health and aging: a systems physiology approach

Vascular aging is a gradual process of the circulation that is aggravated by the development of cardiovascular risk factors and affects both the macro- and microcirculation (Nichols et al., 2011). Since aging is the main denominator for chronic CVD manifestations, the concept of vascular aging has been proposed to improve clinical guidance of patients with increased cardiovascular risk (Nilsson et al., 2009, 2013). The concept implies that age-related clinical or subclinical manifestations are associated with vascular alterations, which can be quantified by sensitive non-invasive vascular assessments. Consistent evidence suggests that arterial stiffness is a subclinical, strong and valid vascular biomarker for the quantification of atherosclerosis and grave cardiovascular dysfunction (Salomaa et al., 1995; Laurent et al., 2006; Vlachopoulos et al., 2010a). Arterial stiffness and the impairment of the buffer capacity of large arteries lead to elevated left ventricular afterload and left ventricular hypertrophy and, at later stages, to heart failure, worsening of coronary artery disease and increased risk of stroke (Hamilton et al., 2007). Aortic pulse wave velocity (PWV), acknowledged as the “gold-standard” method for measuring arterial stiffness, is an independent predictor for cardiovascular morbidity and mortality in the general population, elderly subjects and in patients with cardiovascular disease (Laurent et al., 2001; Sutton-Tyrrell et al., 2005; Hansen et al., 2006; Mattace-Raso et al., 2006). An increase of aortic PWV by 1 m/s has been reported to represent a risk increase of 15% in total cardiovascular and all-cause mortality (Vlachopoulos et al., 2010a). In the Baltimore Longitudinal Study of Aging, aortic PWV increased twofold across the age span and higher fitness were associated with reduced arterial stiffness in a predominantly sedentary population as well as in endurance trained older men compared to less active peers (Vaitkevicius et al., 1993). In a population-based study of 373 younger subjects in the Netherlands, it was found that the effect of habitual PA on arterial stiffness depends on its intensity and differs depending on the arterial tree segment. Vigorous but not light-to-moderate habitual PA provides favorable associations with peripheral arterial stiffness in young adults (van de Laar et al., 2011). In our study, different approaches of measuring arterial stiffness are applied in various vascular beds. Central and peripheral PWV measurements are performed as well as 24-h monitoring of central haemodynamics such as augmentation index (AIx) and pulse pressure (PP). Assessment of the macrocirculation includes the structural analysis of the carotid intima-media thickness (IMT).

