### Study procedures and ethical considerations

All participants are briefed verbally and receive information approved by the Ethics Committee of Northwestern and Central Switzerland (EKNZ) giving details on the study procedures, the RCT and the process of randomization. The study will be carried out in accordance to the protocol and with the principles stated in the Declaration of Helsinki and the Guidelines of Good Clinical Practice (GCP) (World Medical Association, 2013). This study protocol was design according the SPIRIT Guidelines.

All measurements and procedures applied in this study are non-invasive. Routine exercise ECG includes an exertional stress test as a medical necessity and safety precaution to evaluate cardiorespiratory health in all subjects. The OSR group undergoes a high intensity walking-based training program. HIIT has previously been applied in a wide range of patients including patients with coronary artery disease. The risk for cardiovascular events has been proven to be equally low for both HIIT and moderate continuous intervention strategies (Rognmo et al., 2012). Retinal vessel analysis includes mydriasis of one eye. Using a mydriaticum (Tropicamid 0.5%), the pupils are dilated and enable retinal vessel analysis. The eye drops can cause temporary discomfort, oftentimes a burning sensation for 1–2 min. Flickerlight exposure can potentially cause slight headaches. The collaborating ophthalmology department in Basel will offer back up at all times in the unlikely event of continuous discomfort.

All participants are committed to sign a consent form and will be informed about their right to withdraw from the study without any consequences. A study assistant will randomize the OSR group in an intervention or a control group by drawing a lot after the last pre-intervention assessment. Participants and investigators are blinded for the group membership during the pre-measurements. All participants are to be recruited from our outpatient department, the Metabolism Unit of the University Hospital Basel, Basel, Switzerland and, in addition, with postings on University webpages and advertisements in local newspapers. We aim to recruit the HOA group in running clubs and on running events in and around Basel. A total of 160 participants will be recruited for the study.

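### The Part II model adjusts only for baseline cfPWV; pre-specifying age and sex as further covariates would be a cheap, modest and conditional gain in precision, not the repair of an error

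*Protocol article*

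**What the plan says.** The Statistical analysis section of the protocol article compares 12-week cfPWV between the two OSR arms by analysis of covariance, "adjusted for the corresponding values at baseline". No further covariate is named. The Sample size calculation section sizes Part II on that same model and "assumed that the correlation between baseline and outcome cfPWV was 0.3".

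Three other places bear on the choice:

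- Potential pitfalls: "Our main outcome (cfPWV) as well as most other vascular measurements are affected by age", followed by haemodynamic variability, lifestyle and circadian fluctuation. The same section says that groups are matched for age and sex. The discussion of limitations applies the age matching to all three groups, which are those of Part I.
- The background section on cardiovascular health and aging reports, from a cited cohort, that "aortic PWV increased twofold across the age span".
- Study procedures and ethical considerations: a study assistant assigns the OSR participants "by drawing a lot after the last pre-intervention assessment". No stratification by age or sex is stated.

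OSR participants are men and women aged 50 to 80 years.

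**The concern.** The plan's stated reason for adjusting is to reduce error variability, yet on its own planning figure the single covariate removes little of it. Age is known before randomisation, spans 30 years in the eligible population and is named as affecting the primary outcome. Neither the stated allocation nor the stated model uses it, and matching concerns the Part I groups rather than the randomised arms.

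In a randomised ANCOVA, a prognostic covariate fixed in advance narrows the confidence interval without biasing the effect, and it takes up chance imbalance that baseline cfPWV does not capture. At stake is some precision in the one part of the study that supports a causal statement. Timing matters: covariates carry confirmatory weight only if they are named before results are seen.

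**Working it through.** **Inputs from the article (Sample size calculation).** Two-sided alpha 0.05; target power 80%; "the expected difference in cfPWV after 12 weeks between OSR in the intervention and those in the control group was 1.0 m/s"; SD 1.5 m/s; baseline-outcome correlation r_b = 0.3; 34 per group, with 80 OSR enrolled in total to allow for dropout.

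**Input not in the documents.** The correlation r_a of age with cfPWV. I assume that it is the same at baseline and at 12 weeks, and take 0.3 to 0.4. No gain from sex is counted, although its degree of freedom is.

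**Step 1: reproduce the plan's figure.**
- Variance removed by baseline: 0.3² = 0.09.
- Residual SD: 1.5 × √(1 − 0.09) = 1.431 m/s.
- Noncentral t with one covariate, error df = 2 × 34 − 3 = 65: power 81.0% at 34 per group and 79.8% at 33.

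The stated 34 is therefore reproduced exactly. If all 40 per arm complete, power is 87.0%.

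**Step 2: what age adds beyond baseline.**

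R² = (r_b² + r_a² − 2·r_b·r_a²) / (1 − r_a²); partial R² = (R² − r_b²) / (1 − r_b²).

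- r_a = 0.3: R² = (0.09 + 0.09 − 0.054) / 0.91 = 0.138; partial R² = 0.053; residual SD 1.392.
- r_a = 0.4: R² = (0.09 + 0.16 − 0.096) / 0.84 = 0.183; partial R² = 0.103; residual SD 1.356.

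**Step 3: power and interval width at 34 per arm.** With baseline, age and sex, error df = 63. The expected half-width is t × SD × √(2/34) × √(1 + k/(68 − k − 3)), where k is the number of covariates. The last factor is the average inflation from chance covariate imbalance: 1.0078 for k = 1 and 1.0239 for k = 3.

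| Model (r_b = 0.3) | Power | Expected 95% CI half-width (m/s) |
|---|---|---|
| Baseline only | 81.0% | 1.997 × 1.431 × 0.2425 × 1.0078 = 0.698 |
| Plus age and sex, r_a = 0.3 | 83.0% | 1.998 × 1.392 × 0.2425 × 1.0239 = 0.691 |
| Plus age and sex, r_a = 0.4 | 85.0% | 1.998 × 1.356 × 0.2425 × 1.0239 = 0.673 |

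The power column leaves out the imbalance factor, as the reproduction of the plan's figure does. It therefore slightly favours the larger model, and the half-width is the fairer measure.

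**Step 4: break-even.** The larger model has the narrower expected interval only if 1 − partial R² is below (1.997 × 1.0078)² / (1.998 × 1.0239)² = 0.968. Age and sex must therefore explain about 3% of the variance left after baseline.

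**Step 5: sensitivity to the planning correlation.** If r_b is 0.7, the residual SD with baseline only is 1.5 × √(1 − 0.49) = 1.071 and the half-width is 0.523. Partial R² for age is then 0.017 at r_a = 0.3 and 0.034 at r_a = 0.4. The half-widths with age and sex are 0.527 (0.8% wider) and 0.523 (unchanged). At a partial R² of 0.01 the interval is about 1% wider than with baseline only.

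**The case against.** The strongest reply is that nothing needs mending. A baseline-adjusted ANCOVA is a standard, unbiased analysis of a two-arm randomised comparison. It is the model on which the sample size rests, and it reaches its target. No stratification factor is stated, so none has been left out of the model. The usual standard error already allows for chance imbalance, and baseline cfPWV carries part of any age effect. An unseen full protocol or SAP could name more covariates. All of this stands, and it makes the point an optional improvement. It does not remove the point, because the article states a specific model and the suggestion is a specific change to it.

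Several stronger readings are tempting, but the documents do not support them:

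- **That precision is certainly lost.** No age-cfPWV correlation is given. The twofold rise describes a cited cohort, with no age span, slope or SD, so a correlation cannot be derived from it without further assumptions. The gain can be zero or slightly negative.
- **That the gain is large.** An age correlation of 0.5 together with r_b = 0.3 would give about 88% power. It would also mean a baseline-outcome correlation within age of only (0.3 − 0.25) / (1 − 0.25) = 0.07. That is hard to square with the good reproducibility that the article reports for cfPWV and with its rule that two readings agree within 1 m/s.
- **That age is the dominant determinant, or that sex matters too.** The article lists age beside other influences without ranking them. Sex appears only as a matching and eligibility characteristic, with no stated effect on cfPWV.

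**Conclusion.** The point holds as a modest, conditional efficiency improvement. On the plan's own correlation of 0.3 and an assumed age correlation of 0.3 to 0.4, adding age and sex takes power from 81% to about 83 to 85% and narrows the expected interval by about 1 to 4% (0.698 to 0.691 or 0.673 m/s). If baseline cfPWV predicts follow-up better than the plan assumes, with a correlation near 0.7, the benefit is about nil and the interval may widen by about 1%.

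A reader might infer that hypothesis 3 is underpowered, biased or wrongly analysed. It is not: the baseline-only model is valid and meets its stated 80%. The case for acting is that the possible gain is larger than the possible loss and that the change costs almost nothing if made in advance.

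**What to change.** In the Statistical analysis section, state that for Part II the 12-week cfPWV will be compared between arms by ANCOVA adjusted for baseline cfPWV, age (continuous) and sex, and that the model with baseline cfPWV alone will be reported as a sensitivity analysis. If a full protocol or SAP already names further covariates, make the documents agree. Leave the sample size at 34 per group, 80 OSR in total. I have calculated nothing for the retinal outcomes, so this recommendation covers cfPWV only.

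The cost is one sentence and two error degrees of freedom (65 to 63 at 34 per arm), with no new data, visits or participants. The downside is an interval about 1% wider if age and sex add almost nothing beyond baseline. The sentence should be fixed before outcome data are seen by arm.
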